## Abstract

**Introduction::**

Persistent psychological distress including symptoms of depression, anxiety, and posttraumatic stress disorder (PTSD) occur in as many as 70% of intensive care unit (ICU) survivors. However, few therapies exist that target this population's unique symptoms and needs. To address this, we developed the Blueprint adaptive coping skills mobile app, which was found to be feasible and reduce psychological distress symptoms in a recent single-center pilot randomized control trial (RCT).

**Objective::**

To describe the methods of the Blueprint 2 multi-center RCT (clinicaltrials.gov ID NCT06538246) being conducted to test the efficacy of the Blueprint app in reducing psychological distress among ICU survivors compared to an education control in a geographically and sociodemographically diverse population, including Spanish-language speakers.

**Methods and analysis::**

In this RCT, 400 participants with a baseline Hospital Anxiety and Depression Scale (HADS) total score ≥8 will be randomized in a 1:1 ratio to intervention or control. The HADS total score at one month post-randomization is the primary outcome. Secondary outcomes include HADS anxiety and depression subscales, posttraumatic stress scale (PTSS), and the quality-of-life EQ-5D 100-point visual analog scale (VAS) at 1, 3, and 6 months. Select subgroup analyses including users of the Spanish-language version of the app will be used to evaluate consistency of effects across patient populations. Constrained longitudinal data analyses will compare outcomes across intervention groups and timepoints.

## Introduction

1.

Cardiorespiratory conditions such as acute respiratory distress syndrome (ARDS), congestive heart failure, myocardial infarction, pneumonia, and sepsis are among the most common ICU diagnoses, as well as the most common causes of morbidity and mortality [1]. Those who survive critical illness also frequently develop the Post-Intensive Care Syndrome (PICS), which consists of impairments across physical, cognitive or mental health domains such as fatigue, insomnia, cognitive dysfunction, depression, anxiety, and posttraumatic stress disorder (PTSD) [2,3]. Psychological distress symptoms are particularly common, with prevalence estimates of PTSD, depression and anxiety ranging from 22% to 70%, and can persist for months to years [4–10]. These symptoms are associated with cognitive impairment [11–13], functional status limitations [14,15], frailty [16], as well as worse cardiorespiratory outcomes including mortality [17–29]. As such, psychological and emotional well-being is central to quality of life [30–33].

A major barrier to addressing these symptoms among ICU survivors is the lack of evidence-based interventions that are easy to access and relevant to their experience [34]. An additional challenge is the historically limited representation in RCTs from patients from certain racial and ethnic communities, including people whose first language is not English [35]. To fill this gap, we developed Blueprint, an adaptive coping skills training (CST) intervention. We have optimized Blueprint through years of research, from a months-long telephone-based program tested in a single center pilot study [36], to a telephone- and web-based version tested in a multicenter RCT (CSTEP) [37], to a completely self-directed and mobile app-based version evaluated in a recent Blueprint pilot RCT [38] (Fig. 1). Throughout these studies, the intervention has consistently reduced symptoms of distress among patients with elevated baseline symptoms. In this study, the fully app-based Blueprint intervention will undergo a formal test of efficacy for the first time in a population that is geographically diverse and includes English- and Spanish-language speakers, the latter of whom will be utilizing our first Spanish-language version of the intervention. Here, we describe the design, methods and planned efficacy analyses of the Blueprint 2 RCT (clinicaltrials.gov ID NCT06538246).

## Materials and methods

2.

### Human subjects and regulatory oversight

2.1.

All procedures for Blueprint 2 RCT, including informed consent, were approved by the Duke University central IRB (cIRB, Protocol ID Pro00115623) and approved by local IRB sites at Oregon Health & Science University (OHSU), the University of Colorado (CU), and the University of California- Los Angeles (UCLA) prior to study initiation. An independent data safety and monitoring board (DSMB) was established prior to study initiation to review and approve the protocol and safety monitoring procedures; subsequent reviews of study activities and data collection occur semi-annually. For this study, adverse events (AEs) are defined as any new HADS score ≥ 18 when previous scores were < 18 and any suicidal ideation that is reported to study personnel. Serious adverse events (SAEs), including those that are fatal; life-threatening; persistent, significantly disabling, or incapacitating; that result in inpatient hospitalization or emergency room visits exceeding 24 h in duration; and/or create a persistent or significant disability will be reported to the DSMB, the cIRB, and National Heart, Lung, and Blood Institute (NHLBI) program officer.

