### Experimental condition allocation

2.5.

Within 48 h post-discharge, all enrolled participants are prompted by the mobile app to complete the HADS survey within the app. Patients with elevated HADS total scores (≥8) are stratified by language (English or Spanish) and auto-randomized within language group by the platform in a 1:1 group ratio using an adaptive, biased-coin minimization method to balance study site and the HADS total scale score < 20 vs. ≥20 in treatment group allocation [40]. This algorithm is programmed directly within the mobile app platform; details of the algorithm are in Appendix A of the Supplemental Material. After completing the baseline survey, the assigned Blueprint or Education Program content auto-populates the app platform and prompts program initiation.

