### Sample size and power considerations

2.13.

We estimated power based on means, standard deviations, and within-patient scale correlations over 6 months derived from our recent RCTs conducted with >500 patients as well as from the recent literature [37,38,46,53,61]. We originally planned to enroll 530 participants to randomize 400. However, due to a lower observed than estimated randomization rate in enrollment after study initiation (45.7%), we increased the target enrollment. We now estimate we will need to enroll ~875 patients to sufficiently safeguard against dropout before baseline and low post-discharge HADS scores at baseline to randomize 400. We conservatively assume 19% cumulative post-randomization dropout by 1 month, leaving 324, as well as an additional 15% dropout between 3 and 6 months [37,38,46]. Assuming a baseline standard deviation of 8.7 and correlation between baseline and 1 month of 0.4, this sample size will provide 90% power with an alpha of 0.05 to detect a treatment group difference of 2.6 units in the 3 month HADS total score, which represents an enduring effect difference similar to the minimal clinically important difference [62–64] in a comparison of two means via repeated-measures analysis. This will also provide 99% power with an alpha of 0.05 to detect a 2-unit difference in the primary outcome, the HADS total score at 1 month, as well as a 3.8-unit difference in the PTSS secondary outcome [61,65]. For subgroup analyses, in a comparison of two means in a repeated-measures analysis between baseline and 3 months, assuming a standard deviation of 4.5 and correlation between baseline and 3 months of 0.5, we will have 80% power with an alpha of 0.02 (to reasonably account for multiple comparisons) to detect group differences in the HADS total score of 4.2 units with a subgroup n of 100, 5.6 units with an n of 80, and 6.0 units with an n of 60, effects similar to those seen in the Blueprint 1 pilot RCT [38]. Power calculations were conducted via the comparison of two means in a repeated measures design in PASS (NCSS, Kaysville, UT).

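### The HADS-based adverse event cannot register sustained worsening in participants who enter at 18 or above, so its counts describe only those entering at 8 to 17

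*Protocol article*

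**What the plan says.** The protocol article, section 2.1, defines adverse events as two things. The first is "any new HADS score ≥ 18 when previous scores were < 18". The second is "any suicidal ideation that is reported to study personnel". Serious adverse events are listed separately and do not depend on HADS; they include those "that result in inpatient hospitalization or emergency room visits exceeding 24 h in duration". After the DSMB's initial approval of the protocol, "subsequent reviews of study activities and data collection occur semi-annually".

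Section 2.5 sets the entry range: "Patients with elevated HADS total scores (≥8) are stratified by language". No upper limit is given there or in Table 1. The minimisation is meant "to balance study site and the HADS total scale score < 20 vs. ≥20 in treatment group allocation".

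Section 2.10 gives the HADS range as 0 to 42 and schedules it in both arms at baseline, in each of the four intervention weeks, and at 1, 3 and 6 months.

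**The concern.** A baseline score exists for every randomised participant and precedes every follow-up score. Someone who enters at 18 or above therefore already has a previous score that is not below 18, and the condition in the definition fails from the start. A rise from 18 to 42 is not an adverse event, while a move from 17 to 18 is. The article gives no other criterion for worsening distress.

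The participants left out are the most distressed at entry. If the count of HADS-based events is read as describing the whole sample, deterioration in this group goes unrecorded under that heading, and the DSMB would not see it from the adverse event count.

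**Working it through.** **The rule against the entry range.** There is no stated figure to reproduce; this part is logic.

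- Entry: HADS 8 to 42 (section 2.5; scale range from section 2.10).
- Event: a score of 18 or more, with previous scores below 18 (section 2.1).
- Reading A, all earlier scores must be below 18 (the plural as written): for baseline 18 or above the probability of the event is 0, whatever happens later.
- Reading B, only the immediately preceding score must be below 18: the event is possible, but only after a fall below 18 and a re-crossing. A score that stays at 18 or above and rises never qualifies.

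**How many are affected.** Inputs: N = 400 and baseline SD 8.7 (section 2.13). The mean is not given, so it is varied. The share is P(HADS ≥ 18 | HADS ≥ 8).

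(a) Normal with SD 8.7 before truncation, cut at 7.5 and 42.5, with 17.5 as the boundary for 18 or above:

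| Underlying mean | Implied sample mean (SD) | Share ≥ 18 | Of 400 |
|---|---|---|---|
| 8 | 14.6 (5.3) | 26% | 105 |
| 12 | 16.3 (6.1) | 38% | 151 |
| 16 | 18.5 (6.8) | 52% | 206 |
| 20 | 21.2 (7.4) | 66% | 265 |
| 22 | 22.7 (7.6) | 73% | 292 |

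This treats 8.7 as the SD before the entry cut, so the implied SD among those randomised is smaller than the plan's figure.

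(b) Gamma shifted to start at 7.5, with SD 8.7 in the randomised sample itself: the share is P(G > 10), where G has mean (sample mean − 7.5) and SD 8.7.

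| Sample mean | Share ≥ 18 | Of 400 |
|---|---|---|
| 14 | 22% | 87 |
| 16 | 31% | 123 |
| 18 | 41% | 165 |
| 20 | 53% | 211 |
| 22 | 65% | 259 |

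**What the rule would miss.** An illustrative simulation used six post-baseline scores, underlying means of 14, 18 and 22, correlation 0.4 or 0.7, and no shift in the underlying mean. Among entrants at 18 or above:

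- Reading A: 0 events in every scenario.
- Reading B: 36% to 75% had an event, all by falling below 18 and crossing again.
- 40% to 59% had at least one score 5 or more points above baseline. None of these counts under reading A.

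That last figure arises with no true deterioration, so it shows how noisy individual change is as well as what goes uncounted.

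**Why 2.6 units is not a usable individual cut-off.** With SD 8.7 and correlation 0.4 (section 2.13), the SD of individual change is 8.7 × √(2 × (1 − 0.4)) = 8.7 × √1.2 = 9.5. With no true change, P(rise ≥ 2.6) = 1 − Φ(2.6 / 9.5) ≈ 39%. For a rise of 3 or more whole points it is about 38% to 40%, depending on continuity correction. The figure is lower at high baselines because of regression to the mean.

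**The case against.** The strongest reply is that a new crossing of a threshold is an ordinary incident-event definition, approved with the protocol, and that distress above 18 is watched in other ways. Suicidal ideation is an adverse event at any score, serious adverse events do not depend on HADS, and HADS itself is the primary outcome, compared by arm. The layout and denominators of safety tables also belong in a statistical analysis plan or DSMB charter that is not shown.

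Much of this stands, and it limits the point. A reader might infer that the trial's safety comparison is blind to worsening in the most distressed participants, or that adverse event rates are diluted by people who cannot have the event. The article does not support either: it describes no between-arm safety comparison, no rate and no denominator, and the other two safety routes remain open. A reader might also set the one-point move from 17 to 18 against the 2.6 units that section 2.13 calls "similar to the minimal clinically important difference". But 2.6 is a difference between group means at 3 months, not a threshold for one person's deterioration.

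What does not stand is that the other routes fill the gap. Suicidal ideation and serious adverse events are different signals from worsening symptoms. The efficacy models in section 2.12 estimate mean differences, the subgroups listed there do not include baseline severity, and statisticians are masked to arm until the final analysis (section 2.11). The mid-week check-in in section 2.7 responds to rising scores at any level, but it is described only for the Blueprint arm and is not safety reporting. Nor is this a detail left to another document: the rule is stated, and it does not fit the stated entry range.

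**Conclusion.** The point holds for the HADS-based component of the adverse event definition and no further. Under either reading that component cannot register sustained worsening in anyone who enters at 18 or above; under the plain reading it cannot occur in them at all. Its counts then reflect only those who enter at 8 to 17 and should not be read as a rate for the whole sample.

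The logic needs no assumption beyond the choice of reading. The size does: the baseline mean and the shape of the distribution are assumed, and the shares run from about 22% to 73% of the 400, or roughly a quarter to two thirds or more. Minimising at 20 shows that the trial expects entrants above the threshold but does not show how many. The point is worth acting on because it concerns safety monitoring and recruitment is still under way (section 2.10 data continue to accrue; section 2.4 plans recruitment to October 2027).

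**What to change.** 1. Reconcile the definition in section 2.1 with the entry range in section 2.5. Say whether previous scores means all earlier scores or only the last one, and how worsening in participants who enter at 18 or above is to be handled. This review does not choose a threshold; that is for the sponsor and DSMB, with the IRB.
2. In DSMB and final safety reports, give the HADS-based adverse event by arm with the denominator restricted to participants with baseline below 18.
3. For participants with baseline 18 or above, tabulate by arm the change from baseline and the proportion worsening at each scheduled HADS. Read this as a between-arm comparison, because individual change is noisy and some apparent worsening is expected in both arms. The sponsor and DSMB should set the worsening cut-off and should not borrow the 2.6-unit group difference.

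The scores are already scheduled in both arms, so no new assessment is needed. The cost is a slightly longer report. By-arm tables for the DSMB can use coded arm labels, or be prepared by the data managers who already see the allocation, so that the statisticians stay masked as section 2.11 requires.

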### Study objectives

2.2.

The aims of this study are to test the efficacy of Blueprint on improving symptoms of depression, anxiety, PTSD, and quality of life among cardiorespiratory failure survivors and to determine which patient-level characteristics are associated with a greater treatment response among sociodemographic subgroups of interest.

### Study design

2.3.

This five-year, multi-center study employs a parallel-group, RCT design to evaluate the efficacy of Blueprint, a four-week behavioral intervention in a geographically diverse and English- or Spanish-speaking population (Fig. 2). Participants are randomly assigned to either the intervention group (Blueprint) or to the control group (Enlighten Recovery), which receives educational materials only [39]. The duration of the study for participants is 6 months from randomization (i.e., baseline), with data used in primary and secondary analyses collected at baseline, 1 month (primary endpoint), 3 months, and 6 months post-randomization. Data will also be collected weekly during the 4-week intervention (at the end of weeks 1, 2, 3, and 4) to trigger additional content for participants with severe or increasing HADS scores and will be used in sensitivity analyses. Both intervention and control content are delivered and outcome data are collected through the same mobile app platform. From the date of first patient enrolled, we estimate it will take 41 months to complete data collection (35 months to enroll 600 participants with an additional 6 months to complete follow-up) and 8 months to perform all final data analyses (primary and secondary outcomes models followed by exploratory and sensitivity analyses) and manuscript preparation.

### Recruitment and eligibility

2.4.

Recruitment began October 15, 2024; as of manuscript publication date, recruitment is ongoing with a planned end date of October 15, 2027. Participants are being recruited from hospital ICUs affiliated with the following academic centers: Duke, OHSU, UCLA, and CU. Clinical research coordinators (CRCs) use local electronic medical records (EMRs) to screen patients in ICUs and stepdown units for potential eligibility and then approach for recruitment before hospital discharge. During the screening and consent process, the CRC provides an overview of the trial, shows a 2-min animated video created to explain the trial, and, if the patient is interested in participating, obtains their informed consent. We plan to consent 875 individuals to randomize 400 participants. Eligibility criteria, which is assessed in two stages (i.e., before and after discharge) can be found in Table 1.

### Experimental condition allocation

2.5.

Within 48 h post-discharge, all enrolled participants are prompted by the mobile app to complete the HADS survey within the app. Patients with elevated HADS total scores (≥8) are stratified by language (English or Spanish) and auto-randomized within language group by the platform in a 1:1 group ratio using an adaptive, biased-coin minimization method to balance study site and the HADS total scale score < 20 vs. ≥20 in treatment group allocation [40]. This algorithm is programmed directly within the mobile app platform; details of the algorithm are in Appendix A of the Supplemental Material. After completing the baseline survey, the assigned Blueprint or Education Program content auto-populates the app platform and prompts program initiation.

### Participant engagement and retention plan

2.6.

The mobile app platform used by both groups has built-in system-generated mechanisms to prompt participants to complete app-related activities. Within 48 h of discharge, participants receive a notification on their device to start using the application. The self-directed program delivers timed alerts on the device home screen to prompt use thereafter. Following the four-week intervention, participants in both arms receive messages to complete 1, 3, and 6 month surveys and every week thereafter until the survey is completed. Although participants can choose to remove the app from their mobile phones, unless they have requested to withdraw or temporarily change to an inactive status, they continue to receive automated text notifications. For participants who fail to initiate or continue app usage, CRCs are prompted to follow up using a protocolized text- and phone-based strategy.

### Blueprint intervention

2.7.

The Blueprint intervention is divided into four week-long blocks focusing on different cognitive-behavioral strategies to assist participants in coping with post-ICU challenges, including feelings of anxiety, depression, and isolation. The content is arranged thematically across the four weeks, a duration shown to be equally efficacious as longer programs [41,42]. Participants are guided to create personalized action plans to aid in their gradual reintegration into daily activities, emphasizing both physical rehabilitation and psychological well-being.

Weekly themes: Week 1 includes *progressive muscle relaxation* as a way to cope with stress, pain, and fatigue and *pleasant imagery* to aid in managing emotional distress related to physical symptoms [43]. During Week 2, participants are encouraged to gradually increase activity through *activity-rest cycling* in which demanding activities are broken up into periods of moderate activity and rest [44], and to engage in *pleasant activity planning*. During Week 3, participants learn how to *cope with unhelpful automatic thoughts* during recovery by recognizing the relationship between thoughts, feelings, and behavior and then replacing unhelpful thoughts with more positive thoughts. A brief in-the-moment relaxation technique called *fast relax* is also taught. During Week 4, patients are trained in a systematic method of problem-solving and developing plans for *using Blueprint skills in real life situations* [45].

Content: Each week's key concepts are introduced by an animated video (Fig. 3). Actual patients who have previously been hospitalized for cardiorespiratory failure describe coping strategies (the “I've Been There” feature) in 2–4 brief videos each block, each approximately one minute in length. In the “2 Minutes with an ICU Doctor” segment, clinicians contextualize adaptive coping within recovery and normalize the process. Each week's coping skills are illustrated through interactive exercises that mimic common daily situations and stressors. The ‘mid-week check-in’ prompts a HADS survey, with ~1 min video content recapping the week's content and encouraging participants to practice it displayed in response to severe (>15) or increasing (i.e., higher than the prior week) scores. Overall, participants are prompted to engage in primary intervention activities 2 to 4 days each week with no single activity requiring more than 10 min. In addition to the primary app content, supplementary app activities are made available, including additional video content and guided practices. A 36-page Blueprint workbook sent to participants post-randomization provides complementary material, exercises, and QR code links to app content (Fig. 4), mailed to each recipient and available as a PDF.

### Education control

2.8.

The control arm, which we call Enlighten Recovery, is an education program [37,46] we developed that contains cardiorespiratory condition-specific content, informed by research on informational needs and past successful education programs [47–49]. Participants who have been randomized to this arm are prompted via automated alerts to use the mobile app. Participants receive educational materials about cardiorespiratory conditions, recovery, and health management post-ICU; this information does not incorporate specific behavioral strategies or support mechanisms. Each week, participants are directed to watch a 3 to 5 min informational video related to the week's content and to complete the HADS survey. The time commitment for the Enlighten Recovery arm is less than the Blueprint intervention by approximately 20 min per week. Similar to the Blueprint intervention, a printed or PDF workbook with QR links to additional videos and educational materials related to each of the four weekly topics is also mailed to participants post-randomization.

